# LIST OF ABBREVIATIONS AND RELEVANT DEFINITIONS

| AE | Adverse Event |
| --- | --- |
| AR | Adverse Reaction |
| CCMO | Central Committee on Research Involving Human Subjects |
| DHA | Docosahexaenoic acid |
| EPA | Eicosapentaenoic acid |
| (F)FA | (Free) Fatty acids |
| IC | Informed Consent |
| IMP | Investigational Medicinal Product |
| Hb | Hemoglobin |
| LPS | Lipopolysaccharide |
| METC | Medical research ethics committee (MREC); in Dutch: medisch ethische toetsing commissie (METC) |
| MRI | Magnetic Resonance Imaging |
| MUFA | Mono-unsaturated fatty acids |
| OGTT | Oral glucose tolerance test |
| PBMC | Peripheral blood mononuclear cells |
| PUFA | Poly-unsaturated fatty acids |
| PWA | Pulse wave analysis |
| Q-PCR | Quantitative real time-polymerase chain reaction |
| (S)AE | Serious Adverse Event |
| SFA | Saturated fatty acids |
| Sponsor | The sponsor is the party that commissions the organization or performance of the research, for example a pharmaceutical  company, academic hospital, scientific organization or investigator. A party that provides funding for a study but does not commission it is not regarded as the sponsor, but referred to as a subsidizing party. |
| SEVR | Subendocardial Viability Ratio |
| TG | Triglyceride |
| WMO | Medical Research Involving Human Subjects Act (Wet Medisch-wetenschappelijk Onderzoek met Mensen) |

# SUMMARY

**Rationale:**

Consumption of high-fat diets can lead to postprandial dyslipidemia, impairment of endothelial function, activation of immune cells and changes in gene expression profiles of immune cells such as peripheral blood mononuclear cells (PBMC).

Recently it was shown that postprandial gene expression profiles of PBMC and plasma triglyceride (TG) and free fatty acid (FFA) responses are dependent on the type of dietary fat consumed (i.e. saturated, monounsaturated and polyunsaturated). Since obese and diabetic subjects usually are in a pro-inflammatory state and have dyslipidemia and endothelial dysfunction we are interested in the effect of different fatty acids in a high load on the PBMC gene expression profiles, plasma cytokine profiles and endothelial function of these subjects.

**Objectives**:

The main objective is to elucidate the acute effects of an oral intake of either saturated, monounsaturated or polyunsaturated fatty acids on PBMC whole genome expression of obese and type 2 diabetic obese subjects.

Secondary objectives are to elucidate the acute effects of the fat loads on PBMC inflammatory response capacity and endothelial function of these subjects. Tertiary objectives are to investigate the effects of the fat loads in the groups of subjects on plasma lipid profiles, plasma glucose and insulin and on monocyte and lymphocyte whole genome expression.

**Study design and study population:**

A single-blind cross-over dietary intervention with subjects (male, 50-70 yrs) with different risk profiles. Twenty-two obese type 2 diabetic subjects will be studied and compared to age and BMI matched healthy obese controls and to age-matched healthy, lean controls.

**Intervention**:

Each participant will consume a high SFA milkshake, a high MUFA milkshake and a high PUFA milkshake after overnight fasting.

**Study outcome:**

The main study outcome is change in PBMC whole genome expression. Secondary study outcomes are changes in inflammatory response capacity and endothelial function. Other study outcomes are plasma lipid profiles, plasma glucose and insulin values and monocyte and lymphocyte whole genome expression.

**Nature and extent of the burden and risks associated with participation, benefit and group relatedness:**

During a screening visit 3 ml blood will be drawn and urine will be collected after a overnight fast and body weight, length, waist and blood pressure will be measured. An oral glucose tolerance test will be performed. A general and medical questionnaire will be used.

During the study period of 8 weeks each participant will visit the university on 3 mornings, separated by at least one week, and will consume within 15 minutes a milkshake containing 95 grams of fat. Blood will be collected and endothelial function will be measured both before consuming the milkshakes (baseline, T=0) and 2 hrs (T=2) and 4 hrs (T=4) after consumption of the shakes. Blood will be drawn by normal venopuncture. At time points 0 and 2 hrs 60 ml blood will be collected and at time point 4 hr 52 ml will be collected, bringing it to a total of 172 ml per day. Hb values of each participant will be monitored during the study to be sure that blood collection will not lead to anaemia.

Participants have to collect a small amount of faeces at one time point during the study period. The body composition of the participants will be measured in the Bod Pod. In addition, the participants will visit the radiology department of the hospital Gelderse Vallei in Ede for a MRI scan to determine their abdominal bodyfat distribution.

The time investment requested from the participants is 1 hour at the information meeting, 2.5 hours at a screening session, 3 x 4.5 hours at the intervention days and 1 hour for the MRI scan. The risks associated with venous blood drawing by venopuncture are minimal. The consumption of the milkshakes is not expected to be associated with discomfort, but could, in rare cases, have adverse effects such as a mild gastrointestinal discomfort (fishy aftertaste in case of PUFA shake, belching, flatulence or loose stools). MRI is a safe procedure, with no known health risk as long as no contraindication is met (see paragraph 9.4.3). MRI can result in a ‘coincidence’ finding. These findings should be reported and subjects will be informed about this.

Studying the postprandial inflammatory response of these subjects will also provide us with more information about development of dyslipidemia and endothelial dysfunction and the influence of fat quality on this.

Phenotyping of the subjects

The phenotype of the subjects can be of importance for their inflammatory response capacity. We will measure some extra parameters for more comprehensive phenotyping of the subjects.

Not only the BMI of a subjects but also the body composition and the location of the fat are important determinants of health (11). Body composition will be measured with the use of the BodPod. Magnetic Resonance Imaging (MRI) will be used to measure abdominal fat distribution, i.e. intra-abdominal fat and subcutaneous abdominal fat.

The human gut flora is a complex microbial ecosystem, which alsoappears to be of key importance in health and disease (12). Therefore, faecal microflora profiling will be performed. Data on bacterial populations of thefaecal flora of the subjects and data about body composition and body fat distribution will give more information about the metabolic phenotype of the subjects.

## 1.2 Study aim:

In the current study we aim to investigate the acute effects of an oral intake of different dietary fatty acids on PBMC gene expression profile in groups with a different risk profile (i.e. healthy lean, healthy obese and type 2 diabetic obese subjects). Three different fat loads of 95 g will be given to the subjects, using either saturated fatty acid (SFA), monounsaturated fatty acids (MUFA) or polyunsaturated fatty acids (PUFA) as basal constituents.

We also aim to investigate the effect of the different fatty acids in the risk groups on inflammatory response capacity, endothelial function, plasma lipid profiles, plasma glucose and insulin levels and monocyte and lymphocyte gene expression profiles.

# OBJECTIVES

The objectives are formulated to elucidate the effects of the different fatty acids in the high fat loads on gene expression of PBMC in type 2 diabetic subjects compared to healthy obese and healthy lean subjects. The main objective of this study is to elucidate whether the high fat loads (containing either SFA, MUFA or PUFA) will have different effects on PBMC gene expression in the three risk groups of subjects. Secondary objectives are to elucidate the effects of the fat loads in the different risk groups on inflammatory response capacity and endothelial function. Tertiary objectives are to investigate the effect of these fat loads in these subjects on plasma lipid profiles, glucose and insulin and monocyte and lymphocyte gene expression profiles. For more comprehensive phenotyping of the subjects we will also measure body composition, bodyfat distribution and fecal micro flora.

## 2.1 Research questions and hypotheses

1. Can intake of high fat loads with different fatty acids (SFA, MUFA, PUFA) result in differential changes in **PBMC gene expression** in the different groups of subjects?

 *The PBMC gene expression profiles of the high risk subjects will be more affected compared to gene expression profiles of the healthy subjects.*

2. Can the **PBMC inflammatory response capacity** be influenced by fatty acid intake and will these changes be different for the high risk subjects?

* Obese and type 2 diabetic subjects will have an impaired inflammatory response capacity. The different fatty acids will differently influence this inflammatory response capacity*

3. Can intake of high fat loads with different fatty acids result in differential changes in **endothelial function** and will these changes be different for the high risk subjects?

 *The different fatty acid compositions of the shakes will result in different changes in endothelial function. The high fat load will result in a higher degree of endothelial dysfunction in the high-risk subjects compared to the healthy subjects.*

# 3. STUDY DESIGN

## 3.1 Intervention study

This study is a single-blind cross-over intervention (challenge) study, planned to run from the end of October till half December 2009.

In this study obese type 2 diabetic subjects will be studied and compared to age and BMI matched healthy obese controls and to age-matched healthy lean controls.

A total of 22 type 2 diabetic obese men, 22 obese men and 22 lean men will consume high-fat milkshakes containing 95 g of fat, mainly consisting of either SFA, MUFA or PUFA. No differences can be seen or tasted between the shakes.

The 22 type 2 diabetic obese, 22 obese and 22 lean men will be randomly divided in 6 groups to determine in which order they will receive the milkshakes. The groups will receive a different high-fat shake every two weeks (see table 1). There will be a minimal period of one week between two testing days, in order to exclude carry over effects. Six persons will be evaluated on each testing day.

Table1: Experimental study design

|  |  | Week 1/2 | Week 3/4 | Week 5/6 |
| --- | --- | --- | --- | --- |
| Intervention order | Group 1 | SFA | MUFA | PUFA |
| Group 2 | SFA | PUFA | MUFA |
| Group 3 | MUFA | SFA | PUFA |
| Group 4 | MUFA | PUFA | SFA |
| Group 5 | PUFA | SFA | MUFA |
| Group 6 | PUFA | MUFA | SFA |

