# 4. STUDY POPULATION

## 4.1 Population

Twenty obese, type 2 diabetic Caucasian men (BMI>30 kg/m2), age 50-70 yr.

Twenty-two healthy obese Caucasian men (BMI>30 kg/m2), age 50-70 yr

Twenty-two healthy, lean Caucasian men (BMI18-25 kg/m2), age 50-70 yr

Subjects must meet all eligibility criteria for inclusion, including participation in a screening OGTT (not for diabetic subjects), to be able to exclude non-treated diabetics.

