### 4.3 Inclusion criteria:

All subjects:

- Male sex
- Age 50-70 years
- Hemoglobin levels>8.4 mmol/L

For diabetic patients only:

- BMI > 30 kg/m2
- Must be on sulphonylurea- or metformin therapy for at least 6 months with a constant dose for at least two months, or on dietary treatment for at least 6 months
- Well-controlled diabetes: fasting plasma glucose concentration must be <10.0 mmol/l at the time of screening.

For obese controls only:

- BMI > 30 kg/m2
- normoglycemic according to WHO criteria (OGTT, fasting blood glucose< 7 mmol/L, after 2 hr <7.8mmol/L)
- Urine glucose concentrations <0,25 g/l
- systolic blood pressure <160 mmHg or diastolic blood pressure < 100 mmHg

For lean controls only:

- - BMI < 25 kg/m2
- normoglycemic according to WHO criteria (OGTT, fasting blood glucose< 7 mmol/L, after 2 hr <7.8 mmol/L)
- Urine glucose concentrations < 0,25 g/l
- systolic blood pressure <160 mmHg or diastolic blood pressure < 100 mmHg

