# STATISTICAL ANALYSIS

In this cross-over study, each subject will consume the three shakes and can be used as its own reference.

Analysis of PBMC whole genome expression data will be performed using a Bayesian linear regression model (implemented in the software package LIMMA; [www.bioconductor.org](http://www.bioconductor.org/)). Raw microarray data will be normalized using RMA quantile normalization. Statistically significant changed genes will be identified by student paired t-test followed by a false discovery rate correction (FDR) The latter is used to correct for multiple testing.

Analysis of secondary and tertiary outcome variables (endothelial function, glucose etc.) will be in SPSS version 15.0. Effects of treatment (SFA, MUFA, PUFA) within each risk group (lean healthy, obese, type 2 diabetic) will be tested by repeated measures ANOVA (mixed model) using pre-defined contrasts, i.e. 2 versus 0 hrs and 4 versus 2 hrs. Additionally, incremental areas under the curve will be calculated for all significant altered outcome variables using the trapezoïdal rule and compared between treatments using one-way ANOVA.

Differences between risk groups for each treatment will be tested by one-way ANOVA followed by LSD correction. Additionally, incremental areas under the curve will be calculated for all significant altered outcome variables and compared between risk groups using one-way ANOVA.

An empty ANOVA table providing more information about the analysis is included below.

| Variable | df |
| --- | --- |
| Risk profile (diabetic, obese, control) | 2 |
| Treatment (SFA, MUFA, PUFA) | 2 |
| Time (0,2,4) | 2 |
| Interaction | 8 |
| Error | 579 |

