## 9.2 Recruitment and consent

Subjects will be recruited from Wageningen and surrounding area. An invitation to participate will be sent by email to all eligible men in the database of participants of past scientific studies in the Division of Human Nutrition. If needed, additional recruitment of subjects will take place by advertisement in the University Weekly (Resource magazine) and local newspapers.

For the recruitment of obese (and diabetic) subjects an advertisement will be placed on the website of the Obesity Association ([www.obesitasvereniging.nl](http://www.obesitasvereniging.nl/)). Obese type 2 diabetic subjects will be informed about the study with the help of general practitioners.

Interested participants will be invited for an information meeting organized 6 weeks before the start of the study where the study, requirements for participation and risks will be explained by the Principal Investigator. An information booklet will be provided during this information meeting. Written informed consent will be obtained during a screening visit 4 weeks before the start of the study. In the informed consent we will ask the participants if they want to give permission for anonymous storage of their blood samples for possible additional analyses in the future. We will ask the METC for approval before performing additional analyses.

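### Controls are called age- and BMI-matched, but the protocol only restricts their ranges, and the stated risk-group tests for secondary and tertiary outcomes adjust for neither age nor BMI

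*Protocol*

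**What the plan says.** The Summary and section 3.1 both describe the comparison groups as matched. The Summary has the diabetic men "compared to age and BMI matched healthy obese controls and to age-matched healthy, lean controls", and section 3.1 repeats this almost word for word: "compared to age and BMI matched healthy obese controls and to age-matched healthy lean controls". The claim is therefore age matching for both control groups, and BMI matching for the obese controls only.

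The operative sections say less:
- **Eligibility (4.1, 4.3).** Every group has the criterion "Age 50-70 years". The obese controls are "Twenty-two healthy obese Caucasian men (BMI>30 kg/m2), age 50-70 yr", and the diabetic men have the same open-ended BMI threshold.
- **Recruitment (9.2).** "An invitation to participate will be sent by email to all eligible men in the database of participants of past scientific studies". An obesity association website is used for obese and diabetic men. In addition, "Obese type 2 diabetic subjects will be informed about the study with the help of general practitioners".
- **Screening (6.3.2), randomisation (6.2) and replacement (6.4).** Screening takes men who meet the criteria. Randomisation sets shake order within each risk group. Replacement of withdrawals carries no matching condition.
- **Analysis (8).** For secondary and tertiary outcomes, "Differences between risk groups for each treatment will be tested by one-way ANOVA followed by LSD correction". Incremental areas under the curve are compared between risk groups by one-way ANOVA as well. Gene expression goes through LIMMA with paired t-tests and a false discovery rate correction; no contrast between risk groups is written down.

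**The concern.** The cross-over protects comparisons between shakes, because each man is his own control. It gives no such protection to diabetic versus obese versus lean, since risk group is not randomised. For those contrasts the protocol's safeguards are the shared eligibility ranges and the word *matched*, and no section says how the matching is done: no caliper, strata, ratio, frequency target or order of enrolment. A shared range is restriction. It limits how far apart the groups can be but does not make their distributions alike.

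The stated analysis neither uses a matched structure nor makes up for its absence. Two things are at stake. An age gap, or a BMI gap between the two obese groups, could be read as an effect of risk status. Even with balanced groups, any outcome variance that age or BMI explains stays in the error term.

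**Working it through.** **1. Is there a covariate in the plan's own model?** Section 8 prints an ANOVA table with risk profile 2, treatment 2, time 2, interaction 8 and error 579 degrees of freedom.
- Observations: 66 men × 3 shakes × 3 times = 594, so total df = 593.
- Listed effects: 2 + 2 + 2 + 8 = 14.
- Error: 593 − 14 = 579, exactly as printed.

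The listed terms use every degree of freedom. With age the error would be 578, with age and BMI 577, and with a 22-level matched-set term 593 − 14 − 21 = 558. The table contains none of these.

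**2. What if age differs only by chance?** Assumptions: ages uniform over 50-70, and 20 completers per group (section 4.5).
- SD = 20/√12 = 5.77 years.
- SE of a difference in mean age = 5.77 × √(2/20) = 1.83 years.
- 95% chance limit = 1.96 × 1.83 = 3.6 years (3.4 years with 22 per group).

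Gaps of this size do not inflate the error rate averaged over trials, because the chance age difference is already part of the sampling variation that the test allows for. In simulation with 20 per group, no group effect and a nominal two-sided 5% level (assumed; the protocol states none), the unadjusted t-test rejected in about 5.0% of trials at age-outcome correlations of 0.2, 0.3 and 0.4. What is lost is precision. A covariate with within-group correlation ρ removes a share ρ² of the residual variance: 4%, 9% and 16% at these three values.

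**3. What if there is a systematic gap?** Assume no true group effect and a true mean age gap g. The outcome then shifts by d = ρ × g/5.77 standard deviations. The two-sided 5% t-test has 38 df and non-centrality d × √(20/2). Rejection rates:

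| Gap | ρ = 0.2 | ρ = 0.3 | ρ = 0.4 |
|---|---|---|---|
| 2 years | 5.5% | 6.2% | 7.1% |
| 3 years | 6.2% | 7.7% | 9.8% |
| 4 years | 7.1% | 9.8% | 13.7% |

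A 4-year gap lies beyond the 3.6-year chance limit. Under step 2 it would arise in about 3% of pairs, so the bottom row describes a systematic difference and not ordinary sampling variation.

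**4. Does adjustment remove it?** In a simulation with 22 per group, a deliberately large 5-year gap and ρ = 0.4, the unadjusted test rejected in 20.7% of trials and the test with age as a covariate in 5.1%.

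**5. BMI.** The documents give no BMI spread. The formula in step 3 depends only on the gap in SD units; gaps of 2-4 years are 0.35-0.69 SD. A BMI gap of the same standardised size between the two obese groups, with the same correlations, would give the same rates.

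**The case against.** The strongest reply is that nothing in the protocol shows the groups will differ. All are Caucasian men aged 50-70, and both obese groups exceed the same BMI threshold. Length and weight are taken four weeks before the start, so matching at selection is feasible even though it is not described. Outcomes are largely changes or incremental areas, which remove each man's baseline, and no figure links age within this window to postprandial change. Covariates are also often left to a SAP, which is not shown here.

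Much of this stands, and it rules out several stronger readings that a reader might infer:
- *That the main question is tested by an unadjusted ANOVA.* Section 8 confines that analysis to secondary and tertiary outcomes. For gene expression no between-group contrast is stated, so adjustment is absent there, not ruled out.
- *That each group has its own recruitment channel.* The database mailing is not limited to one group, and the obesity association notice serves both obese groups. Only the general-practitioner route is specific to the diabetic men.
- *That chance imbalance inflates false positives.* Step 2 shows that it does not, on average.
- *That a rate of 10-14% is to be expected.* That needs a systematic gap of about 4 years and a correlation of 0.3-0.4, neither of which the documents give.

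The appeal to a SAP does not fully answer the point. Matching is a step in selecting participants and belongs in the protocol, and the protocol already names a test without covariates.

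**Conclusion.** The concern holds in a limited form. Matching is asserted in two places and carried out in none, and the stated risk-group tests for secondary and tertiary outcomes contain no age, BMI or matched-set term. Shake comparisons within a man are unaffected. The BMI part concerns only diabetic versus healthy obese men, since the lean group differs in BMI by design.

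The size depends on what separates the groups. With chance differences only, the error rate stays at 5% on average, and the cost is the unexplained variance (4-16% for assumed correlations of 0.2-0.4). With a systematic gap, which is possible because diabetic men are also recruited through general practitioners, the pairwise false-positive rate would be about 6-14% for assumed gaps of 2-4 years and the same correlations. These ranges rest on an assumed uniform age distribution, 20 men per group and a two-sided 5% test. They illustrate sensitivity and do not estimate bias in this trial. The case for changing the plan is that adjustment guards against a plausible confounder at almost no cost.

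**What to change.** In section 8:
- Replace the one-way ANOVA between risk groups, including the incremental-area comparison, with a linear model containing risk group and age.
- Fit a separate diabetic-versus-healthy-obese model with age and BMI. It has to be a separate model, because BMI should not be adjusted for in contrasts with the lean group, which it defines.
- Use the same covariates in any between-group LIMMA contrast for gene expression.

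In the Summary and section 3.1, describe the controls as of the same age range and, for the obese controls, of the same BMI range. If matching is actually done at selection, keep the word and state the rule, including how replacements are chosen.

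Cost: one additional model and one or two degrees of freedom. With 60 completers, the three-group error df goes from 57 to 56; with 40 men in the two obese groups it goes from 38 to 36. No new data are needed: age is established for eligibility, and length and weight are recorded at screening.

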## 5.1 Intervention meals

The high-fat shakes the participants will consume on each study day will contain 95 g fat each, and the total volume of each milkshake to be consumed will be 500 ml. The fatty acid composition is the only component that will differ between the milkshakes.

The basal constituent of all three milkshakes will be whipped cream and for every milkshake extra amounts of the specific fats of interest (i.e SFA, MUFA or PUFA) will be added. Water will be added to reach a total volume of 500 ml. For the composition of the milkshakes see table 2.

Table 2 : composition of the shakes

|  | | | **SFA shake** | **MUFA shake** | **PUFA shake** |
| --- | --- | --- | --- | --- | --- |
| Basal constituent (whipped cream) | | |  | | |
| Protein (g) | | | 3 | 3 | 3 |
| Carbohydrates (g) | | | 22 | 22 | 22 |
| Fat (g) | | | 40 | 40 | 40 |
| Extra added fat | | |  | | |
| Fat (g) | | | 55 | 55 | 55 |
|  | SFA (g) | | 45 | 10 | 10 |
| MUFA (g) | | 10 | 45 | 10 |
| PUFA (g) | | - | - | 35 |
|  | Of which EPA/DHA (g) | - | - | 22 |
| **Total** | | |  | | |
| Fat (g) | | | 95 | 95 | 95 |
| Energy (KJ) | | | 3938 | 3938 | 3938 |

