### 6.1.2 Measurements of secondary study outcomes

PBMC immune response capacity

Cytokine profiles will be measured in plasma at all time points (T=0, 2 and 4 hrs) by quantitative immunoassays at Rules Based Medicine laboratories (Austin, Texas, USA). The cytokine profile of a panel of 120 proteins including adiponectin, CRP, and interleukins will be determined. For details on these 120 proteins, see: <http://www.rulesbasedmedicine.com/products-services/humanMAP-antigen.asp>

Plasma levels of additional potential biomarkers for metabolic syndrome (i.e. MBL2, FAM3D) will be measured in plasma by ELISA.

PBMC immune response will be determined by stimulation of the isolated cells ex vivo with lipopolysaccharide (LPS) for 4 hours. TNFα secreted in culture medium of the PBMC will be measured by ELISA. PBMC expression of genes involved in the acute immune response will be measured by qPCR.

Leukocyte activation markers will be determined at all time points (T=0, T=2, T=4 hrs) by using flow cytometry analysis (coulter Epics XL.MCL flow cytometry by Beckman Coulter).

Endothelial dysfunction

Macro vascular regional arterial stiffness will be assessed by Pulse Wave Analysis (PWA) (13). This is a non-invasive measurement which will be performed at every time point (T=0, 2 and 4 hrs).

A pressure sensor (applanation tonometer) is applied on the radial artery to record pressure pulse waveforms. The waveform is calibrated using systolic and diastolic pressure values from a conventional cuff measurement. From these peripheral waveforms we can derive a aortic pressure waveform and conduct a pulse wave analysis (PWA). A number of features can be extracted from a PWA, which cannot be made from the conventional measurement of brachial blood pressure. These features include the Augmentation Index (Aix) and the Subendocardial Viability Ratio (SEVR).

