## 6.2 Randomisation and blinding

Before the start of the study, participants of each ‘risk profile group’ will be randomly allocated to one of the six intervention groups (see table 1). The shakes will be labeled with three different codes. Participants will not know which code is allocated to which shake.

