### 9.4.3 Risks for the participants

There are minor risks for the participants during the intervention. The consumption of the high-fat shakes is not expected to be associated with any risk, although in rare cases it could lead to mild gastro-intestinal discomfort (belching, flatulence or loose stools). Participants also could experience a fatty taste in their mouth after intake of the high-fat shakes, and a fishy aftertaste in case of the PUFA enriched shake. Venapunctures can occasionally cause a local haematoma or bruise and some participants may report pain or discomfort.

The performed functional measurements of endothelial function are non-invasive and risks are therefore minimal.

MRI is a safe procedure, with no known health risk as long as no contraindication is met. These contraindications include persons with the following devices:

- Central nervous system aneurysm clips;
- Implanted neural stimulator;
- Implanted cardiac pacemaker or defibrillator;
- Cochlear implant;
- Ocular foreign body (e.g. metal shavings);
- Insulin pump;
- Metal shrapnel or bullet;
- Or metal containing corpora aliena in the eye of brains

MRI can result in a ‘coincidence’ finding. These findings should be reported and subjects will be informed about this.

Subjects that do not want to be informed about a ‘coincidence’ finding can not participate in the MRI measurement.

The time investment requested from the participants is shown in table 4.

Table 4: Time investment per participant

|  | Time at university/ hospital (OGTT, consumption of milkshakes, blood sampling etc) | Questionnaires | Weight/height /blood pressure | Blood collection during screening | Total |
| --- | --- | --- | --- | --- | --- |
| Information meeting | 1 hour |  |  |  | 1 hr |
| Screening | 2 hours | 15 min | 15 min | 10 min | 2.5 hrs |
| Week 1/2 | 4.5 hours |  |  |  | 4.5 hrs |
| Week 3/4 | 4.5 hours |  |  |  | 4.5 hrs |
| Week 5/6 | 4.5 hours |  |  |  | 4.5 hrs |
| MRI | 1 hour |  |  |  | 1 hr |
| Total time whole study | | | | | 18 hrs. |

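### The claim that the shakes taste alike conflicts with the protocol's own warning of a fishy aftertaste from the PUFA shake, and the existing shake codes are withheld only from participants

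*Protocol*

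**What the plan says.** On the shakes themselves, section 3.1 is categorical: "No differences can be seen or tasted between the shakes". Two other places describe a taste effect tied to one shake. The Summary's paragraph on burden and risks lists, among effects that could occur rarely, "fishy aftertaste in case of PUFA shake, belching, flatulence or loose stools". Section 9.4.3 says that participants could experience "a fishy aftertaste in case of the PUFA enriched shake". Table 2 in section 5.1 shows added EPA/DHA in the PUFA shake alone: "Of which EPA/DHA (g) | - | - | 22", where the columns are SFA, MUFA and PUFA.

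On masking, section 3.1 says "This study is a single-blind cross-over intervention (challenge) study". Section 6.2 (Randomisation and blinding) gives the shakes three codes and then says "Participants will not know which code is allocated to which shake". It names no other masked role.

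On the vascular outcome, section 6.1.2 says "A pressure sensor (applanation tonometer) is applied on the radial artery to record pressure pulse waveforms", with a recording at 0, 2 and 4 hours. It does not mention masking of the person who makes the recording.

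**The concern.** Participant masking is the only masking that the protocol describes. The statement that supports it is contradicted by the protocol's own risk text, for one of the three treatments being compared. Table 1 gives each man the PUFA shake once, so every participant is exposed to the possible cue.

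If a participant recognises the PUFA shake, the remaining safeguard would be that the people who measure, process and analyse do not know the allocation. The protocol does not provide for this. That matters most for endothelial function, a secondary outcome with its own research question and hypothesis in section 2.1. It is recorded with a sensor that a person applies to the wrist, and the result is compared between shakes. An operator who knows the shake could, without intending to, let expectation affect how the recording is made.

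**Working it through.** The plan gives no figure to reproduce on this point, so the check is a comparison of texts.

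**Step 1: can the taste statements be reconciled?**

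| Place in the Protocol | Content | Shakes concerned |
| --- | --- | --- |
| 3.1 | No visible or taste difference | All three |
| Summary, burden and risks | Fishy aftertaste possible, listed with rare effects | PUFA only |
| 9.4.3 | Fishy aftertaste possible | PUFA only |
| 5.1, Table 2 | 22 g EPA/DHA in the added fat | PUFA only |

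Section 9.4.3 also mentions a fatty taste, but for the high-fat shakes in general, so that cue does not separate them. The fishy aftertaste does. Section 3.1 allows no exception and nothing elsewhere qualifies it, so the conflict lies within the current text.

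**Step 2: who is masked?** Section 3.1 says single-blind and section 6.2 names participants. Pulse wave operators, laboratory staff and the analyst are not named anywhere as masked. The protocol does not say that they know the allocation either. The supportable statement is that their masking is not provided for.

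**Step 3: which outcomes are exposed?**
- Primary outcome (6.1.1): whole genome microarrays, an instrument reading. Exposure is small.
- Endothelial function (6.1.2): a tonometer applied by an operator. With 3 time points on each of 3 study days (section 6.3.4), that is 3 × 3 = 9 recordings per man. This outcome is the most exposed.
- LPS stimulation, flow cytometry and plasma assays: people handle the samples, but the readings come from instruments.

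**Step 4: can the bias be sized?** No. The protocol gives no variability for the pulse wave indices and no basis for how far operator knowledge might move them. The following is an illustration only. Suppose that knowledge shifts the mean difference between two shakes by δ, with 20 completers in a risk group (section 4.5) and a two-sided 5% paired t-test. The rejection rate when there is no true effect comes from the non-central t distribution with 19 df.

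- If δ is in SDs of the paired difference, the non-centrality is δ × √20.
- If δ is in SDs of a single within-person measurement with independent errors, the difference has an SD larger by a factor of √2, and the non-centrality is δ × √20 / √2 = δ × √10.

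| Assumed δ | Rate, δ in SDs of the paired difference | Rate, δ in single-measurement SDs |
| --- | --- | --- |
| 0.1 | 7.1% | 6.0% |
| 0.2 | 13.6% | 9.2% |
| 0.25 | 18.6% | 11.7% |
| 0.3 | 24.7% | 14.7% |

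No figure in the protocol supports any of these values of δ. Section 8 also plans repeated measures ANOVA, not a paired t-test, for this outcome. The table shows only that a modest systematic shift would raise the error rate above 5%. It is not an estimate for this trial.

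**The case against.** The other side has several fair points.

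- **Single-blind is a declared choice.** Leaving staff unmasked contradicts nothing in the protocol. This stands. The staff half of the point is therefore a cheap improvement; the error in the text is the taste claim.
- **The aftertaste is only possible.** The Summary treats it as rare, and 9.4.3 says only that it could occur. An occasional aftertaste is also not quite the same as shakes that can be told apart while being drunk. This stands as a limit on how often masking would fail. It does not rescue a categorical statement that admits no taste difference.
- **Participant expectation has little to act on.** None of the primary, secondary or tertiary outcomes in section 6.1 is a self-reported efficacy measure. This largely stands, and it is why the weight falls on the measuring staff.
- **Key holding and analyst masking may be settled in an analysis plan or operating procedure that is not shown.** This is possible, above all for the analyst. But section 6.2 is the protocol's own place for saying who is masked, and it stops at participants.

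A reader might infer that the operators do know which shake was given, or that the PUFA comparison has no protection at all. The documents support neither: they are silent on what operators know, and recognition of the shake is only possible. Nor do they describe a subjective step of accepting or rejecting waveforms, so bias by that route would be conjecture. It would also go too far to say that a future report's description of the blinding would be untrue, since the single-blind label would remain correct as a statement of intent.

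**Conclusion.** The concern holds in a limited form. Section 3.1 is contradicted by the Summary and section 9.4.3, and participant masking may fail for the PUFA shake. Masking beyond participants is not provided for, although the codes that would allow it already exist. The consequence is mainly for the tonometry and is small for the microarray primary outcome. The size of any bias is unknown and cannot be worked out from the protocol.

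The conclusion on the taste claim rests on the text alone. The conclusion on staff rests on reading single-blind, together with section 6.2 naming participants only, as leaving other roles without stated masking. The point deserves correction because it is nearly free. It does not put the primary comparison in doubt.

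**What to change.** In section 3.1, replace the claim with a sentence such as: the shakes are matched in appearance and volume, but the PUFA shake may be recognised by a fishy aftertaste.

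In section 6.2 (Randomisation and blinding), add: the key to the three shake codes is held only by the person who prepares and labels the shakes, and is withheld from the pulse wave operators, the laboratory staff and the analyst until the data are locked.

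The cost is two sentences. Shakes, visits, sample size and measurements stay as they are, and the codes are already planned. The small downside is practical: the key must be kept away from the measuring team throughout.
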